### Interventions

Mycophenolate mofetil (CellCept®, Roche Laboratories Inc., Nutley, New Jersey) in 500 mg/tablet will be used in this trial. All adult patients (aged ≥18 years) will be treated with mycophenolate mofetil at the initial dose of 5 g/day, twice daily, while adolescent patients (aged 13–17 years) will be treated with mycophenolate mofetil at the initial dose of 3–5 g/day based on the patient’s body surface area (BSA) at enrollment (i.e., 5 g/day for those with a BSA of > 1.5 m^2^, 4 g/day for those with a BSA of 1.26 to 1.5 m^2^, and 3 g/day for those with a BSA of 1.0–1.25 m^2^). Self-administration of the study drug will take place on an outpatient basis (under parents’ supervision in some cases, as appropriate). Patients will return unused tablets at each follow-up visit; the unused tablets will be counted and recorded to determine compliance. One cycle is considered to be 4 weeks, and the next cycle of the treatment with mycophenolate mofetil will start only after safety assessments are done.

Allopurinol at the dose of 300–600 mg/day will be coadministered orally, twice daily, for blockage of the guanine salvage pathway [23]. All adult patients (aged ≥18 years) will be treated with allopurinol at the dose of 600 mg/day twice daily, while adolescent patients (aged 13–17 years) will be treated with allopurinol at the dose of 300 or 600 mg/day twice daily based on the patient’s body weight at enrollment (i.e., 600 mg/day for those with a body weight of ≥40 kg, and 300 mg/day for those with a body weight of < 40 kg). Evidence in kidney transplant recipients suggests that concurrent administration of mycophenolate mofetil with allopurinol is innocuous [24, 25].

Available palliative and supportive care for disease-related symptoms should be offered to all patients. Palliative radiotherapy is allowed for local pain control, provided that (1) the patient does not have progressive disease, (2) no more than 10% of the patient’s bone marrow is irradiated, and (3) the radiation field does not encompass a target lesion. Surgical resection of the disease is permitted after documentation of response. All the patients will be instructed not to take any other medications (including over-the-counter products) during study participation without prior consultation with the investigators.

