### Study endpoints

The primary endpoint of this trial is progression-free survival (PFS) (or disease control rate (DCR)) at 16 weeks. The secondary endpoints include PFS, overall survival (OS), overall response rate (ORR) (based on the RECIST criteria version 1.1) [20, 21], safety parameters (according to the Common Terminology Criteria for Adverse Events (CTCAE) version 5.0), pharmacokinetic (PK) parameters (i.e., plasma levels of MPA and its metabolites), biomarkers (consisting of lactate dehydrogenase and circulating tumor cells), pain score (using the Thai version of Brief Pain Inventory (BPI) [22]), and quality of life (using the EORTC QLQ-C30 questionnaire version 3.0 and the EORTC QLQ-LC13 questionnaire).

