SV = screening visit; C_x_w_y_ = cycle x week y; FV = final visit. ^(a)^ Lab tests include Na, K, Cl, HCO3, Ca, Mg, P, albumin, AST, ALT, ALP, total bilirubin, direct bilirubin, BUN, Cr, PT, PTT, INR, and LDH; ^(b)^ Blood obtained from the pharmacokinetic study will be used for measurement of circulating tumor cells on C_1_W_0_ and C_1_W_1_ so that no additional blood samples will be collected; ^(c)^ Urine analysis includes a urine pregnancy test for a female patient of childbearing age; ^(d)^ Blood samplings (at 0, 0.5, 1, 1.5, 2, 3, 4, 6, 8, 10, and 12 h); ^(e)^ Additional samplings for drug monitoring may be required when drug dosage is modified (after ≥7 days of drug administration with an adjusted dose level); ^(f)^ Tumor assessment by a computerized tomography (CT) scan (of the chest ± other organs, if required) or magnetic resonance imaging (MRI), done at baseline, 8 ± 1 weeks and 16 ± 1 weeks after initiation of study drug administration; in case of objective tumor response (complete response or partial response), confirmatory imaging studies will be performed at least 4 weeks after initial documentation of response

There are three drug regimens to be used for prophylaxis of possible infection during study participation: (1) ivermectin (12 mg/day) for 2 days before Cycle 1, Week 0 [28], (2) trimethoprim-sulfamethoxazole (160/800 mg/day) once daily from Cycle 1, Week 1, until discontinuation of mycophenolate mofetil [29], and (3) acyclovir (400 mg/day) twice daily from Cycle 1, Week 1, until discontinuation of mycophenolate mofetil [30]. No evidence of PK drug-drug interactions between any of these regimens and mycophenolate mofetil is reported [31].

Should mycophenolate mofetil prove beneficial to some patients (i.e., evidence of stable disease or partial response) at the end of the treatment period (on Week 16), the study treatment will be given to those patients in the extension period until one of the withdrawal criteria is met. Additional visits will be scheduled during the extension period (Table 4).

**Table 4 Tab4:** Additional visits and assessments in the extension period

Procedures	Study Visits								
	C_5_w_2_	C_5_w_4_	C_6_w_2_	C_6_w_4_	C_7_w_2_	C_7_w_4_	C_x_w_2_	C_x_w_4_	FV
Physical examination	×	×	×	×	×	×	×	×	×
Lab test for complete blood count	×	×	×	×	×	×	×	×	×
Other lab tests^(a)^		×		×		×		×	×
Circulating tumor cells	×		×		×		×		
Biobank collection		×		×		×		×	×
Urine analysis^(b)^		×		×		×		×	×
PK study^(c)^									

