### Sample size determination

The sample size was calculated according to the Simon’s minimax two-stage design, with PFS at 16 weeks as the primary endpoint. PFS is dichotomized according to whether PFS is ≤16 weeks (defined as disease control failure (DCF)) or > 16 weeks (defined as disease control success (DCS)). Therefore, treatment with mycophenolate mofetil will be considered successful if the 16-week radiological evaluation indicates stable disease, partial response, or complete response, as defined by the RECIST criteria version 1.1. Patients alive after 16 weeks without signs of progression will be regarded as DCS.

The sample size was calculated under a hypothesis of interest in which DCS at 16 weeks is ≥32% (*p*_1_ = 0.32, the minimal proportion of successes that makes the experimental treatment worth further studies) and a null hypothesis in which mycophenolate mofetil reaches a DCS at 16 weeks < 12% (*p*_0_ = 0.12, the proportion of successes that implies no clinically worthwhile activity of the experimental treatment). Setting *α* = 0.10 (where *α* represents the probability of failing to reject a treatment with response probability ≤*p*_0_) and *β* = 0.10 (where *β* represents the probability of rejecting a treatment with response rate ≥ *p*_1_), this condition requires 19 patients to be enrolled in Stage 1. Recruitment will continue to reach a total of 27 patients if the number of DCS among the first 19 patients is at least 3; otherwise, the trial will be stopped for inefficacy after analysis of 19 patients. As per the study protocol, mycophenolate mofetil will be deemed promising and worth further studies if at least 6 DCS is observed at the end of the study.

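### The 16-week success rule makes no exception for patients given palliative radiotherapy or resection before week 16, so local treatment can add successes to a decision that turns on 6 of 27

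*Protocol article*

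**What the plan says.** All places are in the protocol article.

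- **Interventions, radiotherapy:** "Palliative radiotherapy is allowed for local pain control, provided that (1) the patient does not have progressive disease". Two further conditions limit the share of bone marrow irradiated to 10% and require that "the radiation field does not encompass a target lesion". Tumour sites other than target lesions may therefore be irradiated, with no time limit.
- **Interventions, surgery:** "Surgical resection of the disease is permitted after documentation of response". No time limit is given, and the text does not say whether the initial or the confirmed response is meant.
- **Study procedures, Table 3 footnote (f):** scheduled imaging is "done at baseline, 8 ± 1 weeks and 16 ± 1 weeks after initiation of study drug administration". After an objective response, "confirmatory imaging studies will be performed at least 4 weeks after initial documentation of response".
- **Sample size determination:** "treatment with mycophenolate mofetil will be considered successful if the 16-week radiological evaluation indicates stable disease, partial response, or complete response". The paragraph then adds: "Patients alive after 16 weeks without signs of progression will be regarded as DCS". Neither sentence makes an exception for irradiated or resected patients.
- **Withdrawal criteria:** there is a general criterion for situations that seriously affect endpoint assessment. It names neither treatment and does not say how a withdrawn patient is scored.

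**The concern.** In a single-arm trial no control group absorbs the effect of other treatments. The scoring rule is complete as written: no progression at 16 weeks is a mycophenolate success, whatever local treatment came before.

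Two routes are open:

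- **Radiotherapy.** The bar on target lesions protects measured shrinkage. It does not protect the assessment of progression, which in RECIST 1.1, the standard the protocol adopts, can also come from non-target disease. A painful non-target lesion that would have progressed by week 16 may be held by radiation, and the patient is then scored as DCS. The condition of no progressive disease helps only as far as current imaging or examination supports it. The scheduled scans are at baseline, week 8 and week 16, and no scan is required before radiotherapy.
- **Resection.** A response first seen at week 8 is due for confirmation at week 12 or later. If the first documentation is enough to permit surgery, the confirmatory scan, the 16-week scan or both could follow it and no longer show the drug's effect on the resected disease.

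Both routes favour the drug, and the decision rests on very few patients.

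**Working it through.** **Inputs** (Sample size determination): p0 = 0.12, p1 = 0.32, α = 0.10, β = 0.10. Stage 1 has 19 patients and continues with at least 3 DCS. The total is 27, and the drug is promising with at least 6 DCS.

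**Formula.** With per-patient success probability p,

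P(promising) = Σ (x = 3 to 19) P[Bin(19, p) = x] × P[Bin(8, p) ≥ 6 − x].

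**Step 1: reproduce the design.** At p = 0.12:

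| Stage 1 DCS | Probability | Stage 2 suffices | Product |
|---|---|---|---|
| 3 | 0.2166 | 0.0608 | 0.0132 |
| 4 | 0.1181 | 0.2480 | 0.0293 |
| 5 | 0.0483 | 0.6404 | 0.0309 |
| 6 or more | 0.0202 | 1 | 0.0202 |

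The sum is 0.0936, within α = 0.10. At p = 0.32 the same formula gives 0.9000. An exhaustive search also finds a smallest maximum sample size of 27, and 19/27 with these cut-offs has the lowest expected size among designs of that total. The stated design is correct.

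**Step 2: one patient.** Suppose one stage 1 patient is counted as DCS because of local treatment, and the drug is inactive. The other 18 stage 1 patients then need at least 2 DCS to continue, and the other 26 need at least 5 in all:

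- 2 DCS: 0.2850 × 0.0608 = 0.0173
- 3 DCS: 0.2072 × 0.2480 = 0.0514
- 4 DCS: 0.1060 × 0.6404 = 0.0679
- 5 or more: 0.0558

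The sum is 0.192, about twice the design value. Two such patients give 0.351.

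**Step 3: assumed conversion rates.** The documents give no frequency of local treatment and no share of patients whose only progression would lie in a treated site. Let c be the share of would-be failures turned into DCS, so p = 0.12 + 0.88c.

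| c (assumed) | p | Patients converted if all 27 enrol (27 × 0.88 × c) | Type I error |
|---|---|---|---|
| 0 | 0.120 | 0 | 0.094 |
| 2% | 0.138 | 0.5 | 0.153 |
| 5% | 0.164 | 1.2 | 0.268 |

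**Step 4: price of a stricter count.** If a share of true successes at p1 received local treatment and were recoded as failures at both stages:

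- 5% recoded: p = 0.32 × 0.95 = 0.304, power 0.866
- 10% recoded: p = 0.32 × 0.90 = 0.288, power 0.825

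The design has no power to spare above 0.90, so this loss limits what the stricter count may be used for.

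**The case against.** **Existing safeguards.** Radiotherapy is barred in progressive disease and over target lesions. Growth of a target lesion, or a new lesion outside the field, still counts as failure. Physical examination is scheduled at every visit, and nothing forbids an unscheduled scan. This stands, and it keeps the number of affected patients small. It does not close the non-target route, and it gives no scoring rule.

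**Resection is a narrow route.** It requires a documented response, and the Discussion says objective responses are rare in osteosarcoma. Such a patient was already responding, so surgery can hide only later progression. Enrolled disease is not amenable to curative surgery, so a scan free of all disease would be unusual. If confirmed response is meant, the scenario of surgery before confirmation disappears. All of this stands. What remains is an ambiguity between two passages and its effect on ORR, which will rest on few events.

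**The size is assumed.** This is correct for Step 3. The 12% benchmark comes from seven earlier phase II trials whose rules on palliative radiotherapy are not shown. If they allowed it, part of the effect is already in p0.

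**Stronger readings that the documents do not support:**

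- A reader might infer that pain relief from radiotherapy is also credited to the drug, because pain is a secondary endpoint. The article is silent on how pain scores after radiotherapy are handled. Such a rule commonly sits in an analysis plan, which is not shown.
- A reader might infer that resected patients will be reported as confirmed or complete responders. No passage says so.
- A reader might want both counts to reach 6 before the drug is called promising. That would change the decision rule and carry the power loss in Step 4.

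**Conclusion.** The point holds for the primary endpoint, where it rests on a written rule and not on silence. Local treatment before week 16 is permitted, and the DCS definition counts progression-free patients as mycophenolate successes without exception. The resection part is weaker: it depends on how documentation of response is read, and it concerns few patients.

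The rule is sensitive to single patients: one stage 1 patient misattributed doubles the type I error, from 0.094 to 0.192. The values 0.153 and 0.268 depend wholly on the assumed 2% and 5%, and on p0 being free of the same effect. If no failure is converted, the type I error stays at 0.094. The sample size and cut-offs are correct and need no change. Whether these treatments should be allowed is a clinical matter and is not judged here.

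**What to change.** Leave the clinical permissions and the primary rule of at least 6 DCS as they are, and change the following:

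1. Record the date and site of any radiotherapy or resection. The visit schedules in Tables 3 and 4 list a review of concomitant medications but no item for these treatments, so their capture cannot be assumed.
2. Report a pre-specified sensitivity count beside the primary count. In it, score as disease control failure any patient who, before the 16-week scan, had radiotherapy to a tumour lesion or was resected without a response confirmed on pre-resection imaging. If the two counts fall on different sides of 6, say so in the conclusion.
3. For ORR, accept confirmation of response only from imaging done before resection.
4. Reconcile the Interventions section with Table 3 footnote (f), so that it is clear whether the documented response is the initial or the confirmed one.

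The cost is a few sentences, one or two data items and no added patients. The sensitivity count is conservative: its power falls to about 0.87 or 0.82 if 5% or 10% of true successes are recoded. It should therefore qualify the primary decision and not replace it.

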### Dose modifications

Each patient will be closely monitored for toxicity, and the dose of mycophenolate mofetil may be adjusted according to individual patient tolerance at the discretion of the investigators (Table 1). The dose of mycophenolate mofetil may be reduced by 1–2 g/day or withheld for some Grade 3 or Grade 4 toxicities, whenever clinically needed (Tables 2). All dose-limiting toxicities will be managed following the standard protocol of a participating study site. The dose of mycophenolate mofetil for cycle 1 to cycle 4 of new patients may be reduced, at the discretion of the investigators, by 1–2 g/day, if more than 33% of the former patients experience a dose-limiting toxicity at that dose level and require dose de-escalation after treatment.

**Table 1 Tab1:** Dose de-escalation schema of mycophenolate mofetil

Dose level	Dose of mycophenolate mofetil in adult patients
0 (initial dose)	5 g/day (5 tablets twice a day)
-1	4 g/day (4 tablets twice a day)
−2	3 g/day (3 tablets twice a day)
−3	2 g/day (2 tablets twice a day)
−4	1 g/day (1 tablet twice a day)

Note that the initial dose (dose level 0) of mycophenolate mofetil in pediatric patients is the dose that is adjusted based on the patients’ BSA at enrollment; dose level –x in pediatric patients will be the initial dose–x g/day

**Table 2 Tab2:** Hematological and non-hematological criteria for suggested dose modification of mycophenolate mofetil

Toxicity^(a)^	Hold study treatment	Dose modification
*Hematological criteria*		
Grade 4 bone marrow hypocellular	No^(b)^	Decrease one dose level^(c)^
Grade 4 febrile neutropenia	No^(b)^	Decrease one dose level^(c)^
Grade 4 neutrophil count decreased	No^(b)^	Decrease one dose level^(c)^
≥ Grade 3 of other hematologic toxicities	No^(b)^	Decrease one dose level^(c)^
Sepsis & any Grade 3 infection	Yes until ≤ Grade 2^(d)^	Resume at one dose level lower^(c)^
Sepsis & any Grade 4 infection	Yes until ≤ Grade 2^(d)^	Resume at two dose level lower^(c)^
*Non-hematological criteria*		
Grade 3, except for: delayed puberty, growth suppression, breast atrophy, erectile dysfunction, diarrhea^(e)^, vomiting^(e)^, and AST/ALT increased or other biochemical laboratory abnormalities without any clinically significant sequelae	No^(b)^	Decrease one dose level^(c)^
Any Grade 4 toxicity	No^(b)^	Decrease two dose level^(c)^

^(a)^ If no recovery (until ≤ Grade 2) is noted after 7 days of dose modification of mycophenolate mofetil, that event will be considered as another toxicity requiring one more dose reduction; ^(b)^ Study treatment may be held whenever clinically needed (at the discretion of the PI and study team); ^(c)^ If more than 3 dose reductions are required, study treatment may be discontinued unless there is reasonable evidence of clinical benefit to justify continuation in the study; ^(d)^ If no recovery (until ≤ Grade 2) is noted after a 28-day delay, study treatment will be discontinued unless there is reasonable evidence of clinical benefit to justify continuation in the study; ^(e)^ Only if it occurs despite maximal medical treatment

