### Withdrawal criteria

More than 4 weeks of study drug interruption due to toxicity;Disease progression or any significant deterioration in the health of the patient;Unacceptable toxicity;Occurrence of another illness which precludes further participation in this trial;Significant protocol noncompliance;Development of an illness or situation which would affect assessments of clinical status and study endpoints to a significant degree;Pregnancy;Patient lost to follow-up; orWithdrawal of informed consent.

Patients who withdraw or are withdrawn prematurely will be replaced only if they discontinue during the first four weeks due to reasons other than toxicity.

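### The adolescent de-escalation formula yields zero or negative doses at the lowest levels for 4 and 3 g/day starters, and two rules on toxicity interruptions beyond 28 days contradict each other

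*Protocol article*

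**What the plan says.** All places are in the Protocol article.

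- **Starting doses (Interventions).** "adolescent patients (aged 13–17 years) will be treated with mycophenolate mofetil at the initial dose of 3–5 g/day", set by BSA: "5 g/day for those with a BSA of > 1.5 m^2^, 4 g/day for those with a BSA of 1.26 to 1.5 m^2" (square metres), "and 3 g/day for those with a BSA of 1.0–1.25" (square metres). Tablets are 500 mg.
- **Levels (Dose modifications, Table 1).** Levels 0 to -4 are listed in a column for adults, ending at level -4 with "1 g/day (1 tablet twice a day". The note extends the scheme to younger patients: "dose level –x in pediatric patients will be the initial dose–x g/day".
- **Size of a step (Table 2).** Two levels for Grade 4 infection with sepsis and for Grade 4 non-hematological toxicity. One level for the other rows, including the listed Grade 4 hematological toxicities. Under footnote (a), failure to recover to Grade 2 or lower within 7 days of a dose change counts as a new toxicity and needs one further reduction.
- **Limit on reductions (footnote (c)).** "If more than 3 dose reductions are required, study treatment may be discontinued", with an exception for clinical benefit.
- **Interruptions.** Withdrawal criteria lists "More than 4 weeks of study drug interruption due to toxicity" with no exception. Footnote (d), attached to the two infection/sepsis rows, covers non-recovery "after a 28-day delay, study treatment will be discontinued unless there is reasonable evidence of clinical benefit".

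**The concern.** Table 1 was built for a 5 g/day start, where four steps of 1 g/day end at a positive dose. The note applies the same subtraction to starts of 4 and 3 g/day without shortening the ladder, so the lowest levels stop being doses. The patients affected are the smaller adolescents, on an immunosuppressant, at the point where toxicity has already forced reductions. The trial is multi-center and has no data monitoring committee, so consistent handling between sites rests on the written rules.

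The two interruption rules raise a similar problem. For one and the same patient, one section requires withdrawal and the other allows continuation.

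**Working it through.** **1. Reproduce Table 1.** With 500 mg tablets, n tablets twice a day give n × 2 × 0.5 = n g/day. For n = 5, 4, 3, 2, 1 this is 5, 4, 3, 2, 1 g/day, as printed.

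**2. Apply the note.** Dose at level -x = starting dose - x (g/day).

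| Adolescent start (g/day) | Level 0 | -1 | -2 | -3 | -4 |
|---|---|---|---|---|---|
| 5 | 5 | 4 | 3 | 2 | 1 |
| 4 | 4 | 3 | 2 | 1 | **0** |
| 3 | 3 | 2 | 1 | **0** | **-1** |

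**3. Can these levels be reached?** Steps are one or two levels (Table 2).

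- Level -3 (3 levels): 1+1+1, or 2+1 in either order. From 3 g/day, 3 - 2 - 1 = 0 after two reductions. A single Grade 4 non-hematological event that has not recovered 7 days after its two-level cut produces this sequence through footnote (a).
- Level -4 (4 levels): 2+2 (two reductions), or one two-level and two one-level steps in any order (three reductions). From 4 g/day, 4 - 2 - 2 = 0. From 3 g/day, 3 - 2 - 2 = -1.

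**4. Does footnote (c) prevent this?** It applies to more than three reductions and does not say whether a two-level cut counts as one or two.

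- Level -3 is at most three on either count, so footnote (c) does not apply.
- Level -4 is two or three if reductions are counted, so footnote (c) does not apply. It is four if levels are counted, so footnote (c) applies, but it only permits discontinuation and has a benefit exception.

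**5. The interruption rules side by side.** Table 2 holds drug in the infection/sepsis rows until Grade 2 or lower. Take a patient not recovered at day 28 for whom benefit is claimed. Footnote (d) allows the patient to stay on study. If the hold continues, the interruption passes 4 weeks and the withdrawal criterion applies without exception. Restarting at day 28 avoids that criterion but breaks the hold, because recovery has not occurred. The extension period (Study procedures) also runs only until a withdrawal criterion is met, so it gives no exception either.

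**6. BSA coverage.** The listed eligibility criteria set a minimum age of 13 years and no minimum BSA. Interventions assigns no adolescent starting dose below 1.0 square metres.

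**The case against.** The strongest reply is that these rules are guidance. Table 2 is labelled as suggested, and adjustment is left to the investigators. Table 1's column is for adults, and the note does not say that every adolescent start has all four reduced levels. Zero can be read as no further drug, and unacceptable toxicity is already a withdrawal criterion. If levels are counted, footnote (c) covers level -4.

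Part of this stands. Discretion softens the consequence, and a site is not without any rule. But discretion over whether to reduce does not define what a zero or negative level means. Reading zero as stopping would end treatment for a 3 g/day starter after two or three reductions, whereas footnote (c) raises discontinuation only beyond three and allows continuation on benefit. The value -1 has no reading at all.

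A reader might infer several stronger points that the documents do not support:

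- *That any Grade 4 event costs two levels.* The listed Grade 4 hematological toxicities cost one. Two of them from 3 g/day give 3 - 1 - 1 = 1 g/day, a usable level.
- *That smaller adolescents have no de-escalation path.* Two reduced levels work from 3 g/day and three from 4 g/day.
- *That the BSA bands conflict with another section.* No other section states bands. The limits 1.25 and 1.26 are ordinary two-decimal notation. Below 1.0 square metres is a coverage gap, which the full protocol may close.
- *That the week-16 endpoint is distorted.* Success is judged on progression status at 16 weeks and every dosed patient is analysed. Nothing shows how many patients would be affected or that the decision would change.

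**Conclusion.** The point holds in a limited form. One of the four reduced levels for 4 g/day starters and two of the four for 3 g/day starters are not positive doses. This is a stated formula that fails, not a detail left out of a condensed article. Level -3 can be reached from 3 g/day however footnote (c) counts. That level -4 lies within three reductions rests on the assumption that footnote (c) counts reduction events and not levels, which the text leaves open.

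The interruption rules contradict each other, but only for infection/sepsis holds that have not recovered after 28 days and where benefit is claimed. The missing starting dose below 1.0 square metres is minor.

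It would go too far to say that sites cannot apply the dose rules. They work for adults at every listed level, for adolescents starting at 5 g/day, and at the upper levels for the others. Sample size, error rates and the decision rule are untouched. The passages should still be reconciled, because the affected patients are minors and the correction is cheap.

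**What to change.** - Reconcile Table 1 and its note with the BSA-based starting doses: for each starting dose, state which levels exist and what follows the last one.
- State whether footnote (c) counts reductions or levels, so that a two-level cut is counted in one way only.
- Reconcile the withdrawal criterion on interruptions with footnote (d), so that one rule applies to toxicity interruptions beyond 28 days.
- As a minor addition, make the eligibility criteria and the starting-dose bands agree for adolescents with BSA below 1.0 square metres.

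Which levels, limits and exceptions apply is for the investigators to decide. The cost is a table and wording amendment, submitted to the ethics committees as the article already requires for any modification. No extra patients or procedures are needed.
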